## Abstract

**Background:**

Acute and everyday stress is substantial for the development of mental and physical diseases, therefore it is crucial to get a better understanding of its pathogenesis. Different methods (e.g., Ambulatory Assessment) and stress reactivity paradigms (e.g., Trier Social Stress Test / TSST) in laboratory settings are often used to investigate basic mechanisms of this process. Due to the technological progress of the last years and especially due to children and adolescents growing up with it, the application of these developments in clinical research is reasonable. The aim of this project is to successfully transfer the TSST for children and adolescents into the virtual world, which will be compared to a real TSST situation. Physiological and psychological stress reactions will be analyzed in order to assess similarities and differences. Moreover, it will be investigated whether a Heart Coherence Exercise (HCE) has a stronger influence on coping with acute stress compared to Natural Relaxation (NR).

**Methods:**

This single-center experimental study will examine acute and everyday stress and coping processes in eighty-four healthy children and adolescents between the ages of 11 and 17. For everyday stress, different parameters (e.g., hormonal profiles and mood ratings) as well as a history of stressful life events and utilized coping methods will be recorded and a relaxation exercise will be practiced on a smartphone over 2 days. Regarding the acute stress reaction, the participants will be confronted either with the virtual or the real version of the TSST, followed by the trained relaxation exercise (HCE vs. NR). Physiological (e.g., cortisol and heart rate) and psychological stress markers (e.g., mood and gaze behavior) will be recorded continuously.

**Discussion:**

Studies are sparse using a virtual version of the TSST in children and adolescents. A successful virtual TSST would constitute an economical variant, which would also make it easier to administer it in clinical or population-based samples. Effective ambulatory relaxation exercises would be a useful addition to clinical treatment approaches.

**Trial registration:**

The study is registered in the German Clinical Trials Register since 10 August 2020 (DRKS00022063).

## Administrative information

Note: the numbers in curly brackets in this protocol refer to SPIRIT checklist item numbers. The order of the items has been modified to group similar items (see http://www.equator-network.org/reporting-guidelines/spirit-2013-statement-defining-standard-protocol-items-for-clinical-trials/).

## Introduction

### Background and rationale {6a}

Stressful or traumatic experiences during childhood are among the most important risk factors for the development of a broad range of mental and physical diseases in child and adulthood [1–3]. Strong relationships have been found between the extent of stress experiences in childhood and the occurrence of various disorders in adulthood. These include depression, anxiety disorders, addictions, and personality disorders, but also physical conditions such as cardiovascular diseases, respiratory diseases, obesity, diabetes, pain disorders, and autoimmune diseases [4].

A definable stress reaction manifests itself in different domains: physiological (heart rate, skin conductance, hormone release), psychological (emotional, cognitive, interpretative), and behavioral (attention, arousal, alertness) [5]. In laboratory settings, these markers can be investigated under controlled conditions, e.g., using the Trier Social Stress Test (TSST) where acute stress is triggered effectively [6], both in adults [7] and children [8]. The main components of the TSST are an interview before a non-confirming, neutral panel, and a spontaneous arithmetic task. Within this paradigm, the factors of social evaluation, uncontrollability, and unpredictability trigger a stress response at different levels [7]. For the TSST, there are also already successfully evaluated variations, e.g., for younger [9] or older [10] participants as well as virtual versions [11, 12] for adults. A virtual version of the TSST for younger participants has neither been investigated nor validated and only one successful application has been published for adolescents with excess weight so far [13]. To the knowledge of the authors, an evaluation of the transferability and applicability of a virtual version to children or adolescents has not yet been carried out. The advantages of a virtual version are a good access format for the younger generation, far-reaching context control and reduced resource requirements in the application of the TSST [12]. These benefits may also help to simplify and conduct more accessible research on acute stress reactions and coping mechanisms in children and adolescents in general.

Beyond acute and clearly defined stressful situations, daily stressors should also be considered in the investigation of stress in adolescence and childhood. To minimize retrospective biases, a physiological Ambulatory Assessment (AA) can be used. Several measurements, both hormonal and subjective parameters, can thus be collected in the natural environment of the participant. Of particular interest are, besides the Cortisol Awakening Response (CAR), diurnal profiles of cortisol or alpha-amylase, for example [14].

The counterpart to acute and everyday stress is coping. The extent of the stress experience depends among others on the individual’s ability to cope with stress. There are many possible approaches investigating coping mechanisms in children and adolescents, the positive effects of such stress-reducing methods have already been observed in the acute stress reaction triggered by the TSST. In one study of Domes and colleagues [15], different methods (Internet-Based Stress Management vs. Progressive Muscle Relaxation) trained over several weeks showed a reduction in subjective stress perception. Internet-Based Stress Management even showed significantly lower cortisol release compared to the control group [15]. Very simple and therefore well suited for children and adolescents and simultaneously easily accessible methods are breathing exercises. Despite their simplicity, they often require not only instruction but also regular training until a stressed person can use them well [16]. A variation that does not require much training is a Heart Coherence Exercise (HCE). During this exercise, 5 s of inhalation and 5 s of exhalation are taken over 5 min. It could be shown that such an HCE can improve cognitive abilities and hyperactive behavior among other things [17]. New digital media such as smartphone health apps offer a wide range of choices for stress regulation (e.g., meditation, mood and sleep diaries), even if they are hardly scientifically based [18]. The increased accessibility of technology, especially for the young generation, provides a low-threshold offer for stress regulation which can be of important value. The HCE is already available as a smartphone app and integrated as a breathing exercise in many smartwatches.

### Objectives {7}

The project focuses on the successful transferability of the TSST for children and adolescents from reality to virtual reality (VR) and the effectiveness of a breathing exercise immediately after an acute stress induction. For this purpose, physiological, psychological, and behavioral variables will be collected in order to analyze and compare the increases, decreases, and changes of acute stress reactions in both TSST versions. To examine everyday stress reactions in healthy children and adolescents, the changes in different physiological and psychological stress parameters will also be investigated for 2 days at home.

It is hypothesized that there will be significant increases in physiological stress parameters (cortisol, alpha-amylase and heart rate) and significant changes in psychological stress responses (mood ratings and gaze behavior) to the TSST in vivo and in virtuo. Specifically, it is expected that both the real and virtual stress situation will cause similar stress responses in these variables. Moreover, it is expected that the HCE will cause a significantly greater decrease in these stress parameters compared to Natural Relaxation (NR). Significant associations between changes of everyday psychological (subjective sleep quality, mood ratings, stressful events, and coping skills) and physiological variables (awakening responses and diurnal profiles of cortisol and alpha-amylase) are expected.

**Fig. 1 Fig1:**
[figure not shown]
Overview of study design. HCE, Heart Coherence Exercise; NR, Natural Relaxation; TSST, Trier Social Stress Test; TSST-IV, Trier Social Stress Test in vivo; TSST-VR, Trier Social Stress Test in virtual reality

## Methods: participants, interventions and outcomes

### Study setting {9}

Children and adolescents will be interviewed and tested by psychologists in the research facilities of the Clinic of Child and Adolescent Psychiatry, Psychosomatics and Psychotherapy of the University of Regensburg, Germany. In addition, several surveys will be conducted at home over 2 days using a smartphone app.

### Eligibility criteria {10}

A prerequisite for participation in the planned experiment will be an age between 11 and 17 years. Another inclusion criterion will be sufficient understanding of the German language. Children and adolescents who are or have ever been undergoing psychiatric, psychotherapeutic, or neurological treatment will be excluded as well as participants with current psychiatric disorders. This will be ruled out by conducting a structured clinical interview. Children and adolescents who are taking glucocorticoid-containing medication and / or psychotropic drugs will also be excluded. In addition, children and adolescents with neurological, endocrinological, or immunological (pre-)diseases will be excluded. Further exclusion criteria will be pregnancy / lactation, early pubertal development due to a hormone status deviating from the norm, intellectual impairment (IQ < 85), and attendance in a school for special needs. Before children and adolescents will be invited to participate in the study, a short screening on the phone will be carried out. Here, inclusion and exclusion criteria will be asked for in order to determine a possible exclusion in advance and to minimize the effort for the children and adolescents.

### Who will take informed consent? {26a}

At the first appointment (T1), a detailed explanation of the study will be provided to the children / adolescents and their parents / legal guardians. This will be done orally and a written information will be handed out additionally. Any questions and uncertainties that arise can be clarified immediately with a person from the study personnel. Consent forms will be signed by the participant, the accompanying parent / legal guardian, and a person from the study personnel. All participants will agree upon taking part voluntarily and termination of their participation is possible at any time without giving any reasons.

### Additional consent provisions for collection and use of participant data and biological specimens {26b}

The collected data will serve only scientific purposes. It will be collected and stored pseudonymously. The saliva samples will be numbered consecutively and analyzed in an external laboratory (Dresden LabService GmbH, 01307 Dresden, under the leadership of [name]. [name], Professorship Biopsychology, Technical University of Dresden, Germany). The data of the health app will be stored temporarily on research smartphones of the department until the data is transferred manually by a member of the study personnel. After the data is saved on an extern hard drive, it will be deleted from the smartphone. The coding key for the pseudonyms will be destroyed 1 year after completion of the study, which will make the participant data anonymous. Study data will only be published in anonymous form.

## Interventions

### Explanation for the choice of comparators {6b}

The comparison between TSST-IV and TSST-VR was chosen in order to evaluate the transferability of the TSST into a virtual version, which would provide various benefits (e.g., lower costs and control of context variables). The comparison between HCE and NR serves to evaluate the effectiveness of the guided relaxation exercise after acute stress compared to a natural control condition.

### Intervention description {11a}

After a telephone screening (T0) for checking the inclusion and exclusion criteria, the participants and their parents / legal guardians will be invited to an initial appointment (T1) in our research facilities. Female subjects who are already menstruating will only be tested (AA and T2) in the luteal phase to ensure comparability with the cortisol reactivities to the male subjects [19].

At the first appointment (T1), a detailed briefing for the participants and the parents / legal guardians will be carried out by an experimenter. After answering all upcoming questions and signing the informed consent, an intelligence test and a clinical interview with the participants will be conducted to check the exclusion criteria. Furthermore, the participants will complete questionnaires on puberty status, personality, traumatic experiences, temperament, and behavior. In preparation for the AA, the participants will be instructed in how to use the salivettes (Sarstedt, Nümbrecht, Germany) for collecting saliva samples. Moreover, the usage of the health app including short surveys and the relaxation exercise (developed and programmed in cooperation with the Department of Media Informatics, University of Regensburg) will be explained and demonstrated to the participants. The app was implemented with the integrated development environment Android Studio. The code was written in Kotlin and Java for the target SDK version 29. To develop the questionnaires, the programming library SurveyKit, Version 1.1.0 [20] was used, which is released under the open source MIT License. The application will run on a Samsung A20e with the operating system Android Pie 9.0 installed. Any questions the participant may have regarding the use of the app can be clarified with the experimenter at this point. The first appointment will take approximately 2.5 h.

The AA will take place on two consecutive weekdays. The first saliva sample will be collected simultaneously with the first alarm clock. The participants will receive a notification via the smartphone app to use the first salivette. A timer will be activated and 30 min later the smartphone app will send another notification to use the second salivette. Between the first and second salivette, the participants will receive information about a 20-min time window for breakfast, because they should not eat anything 10 min before the next salivette to avoid contamination. Subsequently, another timer of 15 min will start. Then, the third and last saliva sample for the registration of the alpha-amylase and cortisol awakening responses will be collected. While the salivette should be kept inside the mouth for about at least 2 min, the participants will be asked about their sleep (only during the first salivette) and their mood (during all three salivettes) via the smartphone app. Overall, the AA in the morning will take place within a time frame of about 45 min. During school time (0800–1600 h), no notifications will appear on the smartphone. At 1600, 1800, and 2000 h, a saliva sample will be taken and stressful events since the last survey as well as used coping strategies and the current mood will be queried. In addition, a relaxation exercise will be carried out for 5 min during the survey at 2000 h. One half of the participants will be given the task of performing the HCE (breathing in and out for 5 s each) guided by the app, while the other half will be given the task of remaining calm and relaxing naturally during this time. At the end of the session, the participants will be asked to assess their mood and to give an overall assessment of the day and if there were any technical problems with the smartphone app. This procedure will be repeated the same way on the second day of the AA (Fig. 2).

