#### Secondary outcome measures

The second outcome is the change in stress responses in everyday life. Everyday stress reactions will be recorded in the AA via self-report and endocrinological measures at a total of 12 time points. Important variables will be subjective evaluations of sleep quality and quantity, stress / tension, sadness, anxiety / fear, anger, and aggression. Furthermore, the participants will be asked to report stressful events of the day and which coping skills they have used. Cortisol and alpha-amylase will be assessed to analyze endocrinological awakening responses and diurnal hormonal profiles. In summary, there are several secondary outcome variables: mood, cortisol, alpha-amylase, stressful events, coping skills, sleep quality, and quantity.

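### The morning samples that measure the awakening response are timed from the first alarm, not from actual awakening, so children who wake before the alarm give an attenuated response that the stated timing checks cannot detect

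*Protocol article*

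**What the plan says.** Under Intervention description {11a}, the ambulatory assessment covers two days: "The AA will take place on two consecutive weekdays". On each morning, "The first saliva sample will be collected simultaneously with the first alarm clock". The later samples are timed from that one: "A timer will be activated and 30 min later the smartphone app will send another notification to use the second salivette", and then "Subsequently, another timer of 15 min will start", after which "the third and last saliva sample for the registration of the alpha-amylase and cortisol awakening responses will be collected". The series is therefore 0, 30 and 45 min from the alarm.

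Awakening is what the measure is meant to be anchored to. The objectives expect associations between everyday psychological variables, subjective sleep quality among them, and "awakening responses and diurnal profiles of cortisol and alpha-amylase". The secondary outcomes section says "Cortisol and alpha-amylase will be assessed to analyze endocrinological awakening responses and diurnal hormonal profiles". Statistical methods {20a} plans correlations and regressions of sleep quality and quantity with the hormonal awakening responses.

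The timing checks are in Strategies to improve adherence {11c}: narrow response windows, app reminders about every 3 min, and MEMS caps that record when the sample container is opened. A sleep survey is given with the first salivette. Section {18a} describes it as covering sleep quality and quantity and does not say whether it asks for wake time.

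**The concern.** Alarm and awakening coincide only when the alarm wakes the child. If a child has been awake for 15 min, the nominal zero sample is really a 15-min sample, part of the rise is already over, and the 30- and 45-min samples are shifted too. That child still answers the app and opens the container on schedule, so the morning looks fully adherent.

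Two consequences follow:

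- The average awakening response is understated.
- If children who rate their sleep as poor are more often awake before the alarm, the timing error is correlated with a predictor in a stated hypothesis. Part of any sleep–hormone association could then come from the sampling anchor.

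An analysis plan can correct for this only if wake time was collected.

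**Working it through.** **What the stated checks can see**

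| Situation | First sample relative to awakening | Visible in app or MEMS times? |
|---|---|---|
| Woken by the alarm | on time | nothing to detect |
| Already awake before the alarm | late | no, opening is on schedule |
| Sleeps past the alarm | taken after the alarm, once awake | yes, as a late opening |

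Only early waking escapes.

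**Inputs.** From the protocol: samples at 0, 30 and 45 min, N = 84, α = .05. The protocol gives no figure for this measure. N = 84 comes from an effect size of f = .30 for the stress test and does not enter here except as the number of children. Assumed, because the documents are silent: a linear rise over the first 30 min, a between-child SD (relative to a mean of 1) of 0.6 to 1.0, no true association, a lead time d, and proportions awake early of p_g (sleep quality above the median) and p_p (below it).

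**Attenuation.** For an early waker the measured rise is the true rise × (1 − min(d, 30)/30). The mean understatement is p̄ × min(d, 30)/30, with p̄ = (p_g + p_p)/2. For 10% vs 50% and 15 min: 0.30 × 0.5 = 15%.

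**Induced correlation.** With normally distributed sleep quality split at its median, r ≈ 0.399 × (p_p − p_g) × (d/30) / SD(measured rise). For 10% vs 50%, 15 min and SD 0.6:

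- Variance = 1.36 × (0.7 + 0.3 × 0.25) − 0.85² = 1.054 − 0.7225 = 0.3315, so SD = 0.576.
- r = 0.399 × 0.4 × 0.5 / 0.576 = .14.

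With SD 1.0 the variance is 2 × 0.775 − 0.7225 = 0.8275, the SD is 0.910, and r = .09.

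**False positives.** Simulated share with p < .05, unadjusted:

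| Early wakers, good vs poor sleepers | Lead | Mean rise too low by | Induced r | False positives |
|---|---|---|---|---|
| 10% vs 10% | 15 min | 5% | 0 | about 5% |
| 30% vs 30% | 15 min | 15% | 0 | about 5% |
| 10% vs 20% | 10–15 min | 5–7.5% | .01–.04 | about 5–6% |
| 10% vs 30% | 15 min | 10% | .04–.07 | 7–11% |
| 10% vs 50% | 15 min | 15% | .09–.14 | 13–25% |
| 10% vs 50% | 30 min | 30% | .17–.24 | 35–59% |

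Simulated rates move by about a percentage point between runs. As a check on the fifth row, Fisher's z gives atanh(.14) × √81 ≈ 1.26, and the chance of exceeding 1.96 is then about 24%.

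For scale, N = 84 detects r = tanh((1.96 + 0.84)/9) ≈ .30 with 80% power (two-sided, unadjusted).

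**If the response is summarised as AUC increase.** The protocol names AUC for hormonal stress responses, and its use for the awakening response is an assumption. Take a curve of 10 at awakening, 17.5 at 30 min and 16.5 at 45 min, falling linearly to 13.5 at 90 min.

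- Correct timing: (10 + 17.5)/2 × 30 + (17.5 + 16.5)/2 × 15 − 45 × 10 = 217.5.
- Awake 15 min early (samples 13.75, 16.5, 15.5): 453.75 + 240 − 618.75 = 75.0, or 34% of the true value.

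Leads of 5 and 10 min give 78% and 56%. The linear-rise model is therefore mild, because it ignores the fall after the peak.

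**The case against.** The case on the other side has several parts.

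- **Detail may exist elsewhere.** The article is condensed. The sleep-quantity question may already record wake time, and children were instructed at the first appointment, possibly including what to do on waking early. This stands: it reduces the remedy to a derivation rule if wake time exists. It does not remove the point, because the article itself fixes the alarm as time zero.
- **Alarm and awakening may usually coincide.** Assessment is on weekdays, and many children may be woken by the alarm. This also stands, and it is why no single magnitude can be given.
- **Large error rates need a strong contrast.** The 13–59% figures rest on 10% vs 50% early waking. With 10% vs 20% there is little beyond attenuation. The rates are also unadjusted, whereas {20a} plans false discovery rate correction for multiple comparisons.
- **Home collection is already a stated limitation.** The Discussion concedes limited control, but the measures it lists concern adherence, not early waking.

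A reader might infer three stronger things that the documents do not support. First, that the awakening response is the secondary endpoint. The text says "there are several secondary outcome variables: mood, cortisol, alpha-amylase, stressful events, coping skills, sleep quality, and quantity", and the awakening response is one derived analysis alongside the diurnal profile. Second, that the sleep association is biased as a matter of fact. That needs early waking to be related to sleep quality, and nothing in the protocol shows it. Third, that oversleeping is an equally hidden error. It would appear as a late container opening.

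**Conclusion.** The point holds as a limited one. The protocol uses the first alarm as a proxy for awakening, and none of its stated safeguards identifies a child who was already awake. On such mornings the awakening response is attenuated. The hypothesised association with sleep quality can be biased, but only if early waking is related to sleep quality.

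Size depends wholly on assumptions: under the linear-rise model the mean rise is 5–30% too low, and false positives run from about 5% to 59%, with the upper values needing a fivefold difference in early waking between poor and good sleepers. Neither the frequency nor the lead time of early waking is known from the documents. The primary outcomes, which concern the acute stress test, and N = 84 are unaffected. This is a worthwhile refinement, not a flaw that threatens the trial.

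**What to change.** In {11a} and {20a}:

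1. State that time zero of the awakening response is actual awakening. Take wake time from the morning sleep survey given with the first salivette, and add one item only if the sleep-quantity question does not already capture it.
2. Derive the offset from waking to the first sample and include it as a covariate in the awakening-response analyses.
3. Report, as a sensitivity analysis, the restriction to mornings with an offset below a pre-set limit. It should not be the main analysis: if poor sleepers wake early more often, the restriction removes them disproportionately and narrows the range of the predictor under study.
4. Keep all mornings for the diurnal profile.
5. For participants without a recorded wake time, state the alarm proxy as a limitation.

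The cost is at most one survey item and a derivation rule. Recruitment ran from June 2021 and was due to end by January 2023, and this version dates from September 2022, so a new item would reach only late enrolees. The analysis rule applies wherever wake time exists, and the stated limitation covers the rest.
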